#### Secondary outcomes

2.3.2

Secondary outcome are as follows:

1)TCM symptom: based on the “Chinese Medicine New Drug Clinical Research Guidelines (Trial)” (China Medical Science and Technology Press, 2002), the investigators evaluate the TCM symptom every 3 months using scoring method as summarized in Table 1. The efficacy is assessed at 3 levels: significant improvement, the integral value after treatment decreased by ≥ 70% than the integral value before treatment; partial improvement, the integral value after treatment decreased by ≥ 30% than the integral value before treatment; no improvement, before and after treatment without change or after treatment integral value than the integral value before treatment decreased by < 30%. All results are recorded in the CRF table;2)Karnofsky Performance Status (KPS): the KPS ranking^[16]^ runs from 100 to 0, where 100 is “perfect” health and 0 is death. Practitioners occasionally assign performance scores in between standard intervals of 10. The investigators evaluate the KPS score every 3 months using scoring method as summarized in Table 2. The efficacy is assessed at 3 levels: improved, KPS score increased > 10 points and maintained for more than 4 weeks; stable, KPS score no significant change; worsening, KPS score reduced by < 10 points. All results are recorded in the CRF table;3)ECOG score: the Eastern Cooperative Oncology Group (ECOG) score (published by Oken et al in 1982),^[17]^ runs from 0 to 5, with 0 denoting perfect health and 5 denoting death. The investigators evaluate the ECOG score every 3 months, and the efficacy is assessed using scoring method as summarized in Table 3. All results are recorded in the CRF table;4)European Organization for Research and Treatment of Cancer (EORTC) Breast-Cancer-Specific Quality of Life Questionnaire (EORTC QLQ-BR23)^[18]^: This questionnaire focuses on physical condition and the quality of life of all participants. The investigators evaluate the score every 3 months, and the efficacy is assessed using scoring method. All results are recorded in the CRF table;5)Clinical indicators: Tumor markers (CEA, CA153, CA125, CA199), immune function evaluation (NK, CD3, CD4, CD8, CD4/CD8), chest computed tomography (CT)/magnetic resonance imaging (MRI), and abdominal B-ultrasound are detected to monitor whether there is the tumor recurrence and metastasis. All the participants perform tumor markers check and immune function evaluation every 3 months, as well as chest CT/MRI and ECT every 6 months;6)Safety indicators are carried out to assess drug safety and whether the participants have any adverse reactions. Blood, urine, and feces routine, liver and kidney function, abdominal B-ultrasound, and electrocardiogram are performed every 3 months. If the investigators find any adverse events (AEs), the event should be assessed according to the WHO acute and subacute side effects of the performance and indexing criteria for assessment. All results are recorded in the CRF table.

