### Inclusion and exclusion criteria

2.5

Participants’ inclusion criteria are as follows: The primary BC after surgical treatment, the pathological diagnosis of breast epithelial tumors (BC), ER, PR, and Her-2 immunohistochemical results were negative; no recurrence of metastasis; KPS score ≥ 60 points; aged 18 to 75 years (including 18 and 75 years); no serious organic or functional disorders, no drugs, and food allergy; and willing to receive treatment, observation, and inspection.

Participants’ exclusion criteria are as follow: do not meet the inclusion criteria; patients expected to survive < 6 months; complicated with cardiovascular and cerebrovascular, liver, kidney, hematopoietic system of serious primary disease, and mental illness; breastfeeding, pregnancy, or women preparing for pregnancy; allergies and allergies to a variety of drugs; and participating in other drug subjects.

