### Statistical analysis

2.6

SPSS 18.0 (SPSS, lnc., Chicago, IL), Stata10.0 (StataCorp, College Station, Texas), and other statistical software are used for data analysis with a 2-sided significance level of 0.05, the point estimate, and 95% confidence interval. If the data obey the normal distribution and the variance is homogeneous, data are expressed as the number of cases (n) and the mean ± standard deviation (SD). Before and after treatment at multiple time points, measurement data using repeated measurement of variance analysis and multiple variance analysis are expressed as median (M), minimum (min), and maximum (max). The Kruskal–Wallis H test is used to compare the data between the 2 groups. The numerical variables are measured at multiple time points before and after treatment, and the generalized estimating equations or mixed effect models are used for the classification and sorting variables. If the analysis index is disordered using χ^2^ test, the analysis index is ordered with rank sum test, the 2-way ordered attribute of different data using linear χ^2^ test, and rank sum test. The survival rate is calculated by Kaplan–Meier method (K-M method), and the survival curve is drawn. Multivariate data are analyzed using multiple linear regression analysis, COX regression analysis, trend testing, and so on.

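### The three TCM symptom efficacy levels have no level for a score that rises, so worsening is either unclassified or merged with no change (minor, one secondary outcome)

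*Protocol article*

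**What the plan says.** All references are to the protocol article.

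- **Section 2.3.2, item 1 (schedule):** "the investigators evaluate the TCM symptom every 3 months using scoring method as summarized in Table 1". Table 1 itself is not shown.
- **Section 2.3.2, item 1 (best level):** the text gives "significant improvement, the integral value after treatment decreased by ≥ 70% than the integral value before treatment". This is the top grade of three.
- **Section 2.3.2, item 1 (middle level):** one step down the text gives "partial improvement, the integral value after treatment decreased by ≥ 30% than the integral value before treatment". It sets no upper bound here.
- **Section 2.3.2, item 1 (lowest level):** the bottom grade reads "no improvement, before and after treatment without change or after treatment integral value than the integral value before treatment decreased by < 30", where the cut-off is in per cent. Results go into the CRF.
- **Section 2.3.2, item 2 (KPS):** also three levels, but one of them is for deterioration: "worsening, KPS score reduced by < 10 points".
- **Section 2.5 (eligibility):** the only score threshold for entry is "KPS score ≥ 60 points". No minimum symptom score is required.
- **Section 2.6 (analysis):** methods are listed by type of variable, not by outcome. For measurement data: "Before and after treatment at multiple time points, measurement data using repeated measurement of variance analysis". For ordered categories: "the analysis index is ordered with rank sum test". Generalized estimating equations or mixed models and multiple regression are also listed. None is tied to the TCM symptom score.

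**The concern.** The rule is stated in full, with cut-offs, so this is not a detail left to an unseen analysis plan. Applied as written, the summary has no place to report a patient who gets worse. Patients are followed in a study lasting 2 years, alongside Western treatment that can include chemotherapy and radiotherapy, so some symptom scores may well rise. If they rise more often in one cohort than in the other, the table of efficacy levels will not show it.

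Two smaller gaps belong to the same rule. The middle level has no upper bound. And a percentage of baseline cannot be formed when the baseline is 0, which eligibility does not rule out.

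**Working it through.** There is no stated figure to reproduce, because the point rests on the logic of the rule.

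**1. The rule applied to example scores.** With baseline b and later score a, the relative decrease is r = (b − a)/b. The levels are r ≥ 0.70, r ≥ 0.30, and unchanged or a decrease below 0.30.

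| b → a | r | Level(s) met as written |
|---|---|---|
| 20 → 4 | 0.80 | significant and partial |
| 20 → 6 | 0.70 | significant and partial |
| 20 → 10 | 0.50 | partial |
| 20 → 15 | 0.25 | no improvement |
| 20 → 20 | 0 | no improvement |
| 20 → 24 | −0.20 | none named; no improvement if a rise counts as r < 0.30 |
| 20 → 40 | −1.00 | as above |
| 0 → 0, 0 → 5 | undefined | none |

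Under the generous reading, the rows for 15, 20, 24 and 40 share one level. Under the literal reading, the rows for 24 and 40 have none. Neither reading reports deterioration.

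**2. What the merging does to a comparison (assumed rates).** Take 310 × (1 − 0.20) = 248 per group (section 2.2) and a two-sided 0.05 level (section 2.6). Suppose both groups have 20% significant and 35% partial improvement, with 25% worsening in group A and 5% in group B.

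- *Three levels:* 20/35/45 in both groups. The distributions are identical, so any test rejects only at about its nominal level (simulated: 6%).
- *Four levels:* A is 20/35/20/25 and B is 20/35/40/5.
  - P(B better) = 0.20 × 0.80 + 0.35 × 0.45 + 0.40 × 0.25 = 0.4175.
  - P(A better) = 0.20 × 0.80 + 0.35 × 0.45 + 0.20 × 0.05 = 0.3275.
  - Half the difference is 0.045.
  - The pooled proportions are 0.20, 0.35, 0.30 and 0.15, and their cubes sum to 0.08125.
  - The standard error is √[(1 − 0.08125)/12 × 2/248] = 0.0249.
  - z = 0.045/0.0249 = 1.81, so power is about Φ(1.81 − 1.96) = 0.44, which agrees with simulation (44%).
- *35% against 5% worsening:* simulation gives 4% with three levels and 76% with four.

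The three-level result is true by construction once the improvement rates are set equal. It shows what the rule cannot see, not what will happen in this trial.

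**3. How mixed the lowest level could be (assumed distribution).** If relative improvement is normal with SD 0.40 and mean m, the share of the lowest level that has in fact worsened is Φ(−m/0.40)/Φ((0.30 − m)/0.40). For m = 0.30 this is 0.227/0.500 = 45%. For m = −0.20 it is 0.691/0.894 = 77%.

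**4. Three levels against the change itself (assumed).** With the same SD, a group difference of 0.10 and 248 per group, simulated power for a t-test on relative change against a rank-sum test on three levels is 0.79 v 0.67 at control mean 0.30, 0.80 v 0.68 at 0.20, 0.79 v 0.58 at 0, and 0.79 v 0.42 at −0.20. The gap depends heavily on the assumed mean.

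**The case against.** The strongest reply is that the levels are a response scale. The lowest is labelled as no improvement, a rise is plainly no improvement, and pooling is what such scales do. The section also says the assessment is based on a published guideline. That answers the claim that worsening patients are necessarily unclassified. It does not answer the pooling, and the KPS item shows that the protocol separates worsening when it chooses to.

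Several stronger inferences are open to a reader, and the document does not support them:

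- *The levels overlap.* They do so literally, but they run from best to worst, and taking the best level met removes the overlap.
- *The trial hides deterioration.* Symptom results are recorded every 3 months, and KPS, ECOG, QLQ-BR23, safety tests and adverse events are recorded too. Only this one summary merges worse with unchanged.
- *Patients without symptoms at entry drop out of the comparison.* Nothing says so. Whether a score of 0 can occur depends on Table 1, which is not shown.
- *The analysis loses power and ignores baseline.* Section 2.6 does not tie this outcome to an unadjusted rank-sum test. It also lists repeated-measures analysis of variance, generalized estimating equations or mixed models, and regression, and the choice for this outcome may stand in an analysis plan not shown.

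**Conclusion.** The point holds in a limited form. Item 1 of section 2.3.2 provides no level for an increased symptom score, so worsening is either unclassified or indistinguishable from no change in this summary. That follows from the text alone and needs no assumption.

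Its size in this trial is unknown. The worsening rates, the SD and the mean changes used above are all assumed, and the power figures illustrate direction only. The zero-baseline gap is conditional on Table 1. The point is minor: it concerns one of several secondary outcomes and has no bearing on PFS, OS or the sample size.

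**What to change.** In section 2.3.2, item 1, state four exclusive levels:

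1. decrease of 70% or more;
2. decrease of at least 30% but less than 70%;
3. no change, or decrease of less than 30%;
4. any increase (worse).

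Add that, if Table 1 allows a baseline score of 0, a patient who stays at 0 is graded as no change and any rise from 0 as worse.

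In section 2.6, add one line: the groups are compared on the TCM symptom score itself, by mixed model or regression with baseline score as a covariate, and the levels are reported descriptively. The score is already collected every 3 months. Section 2.1 forms the cohorts by whether patients take TCM, so balance at baseline cannot be assumed. The model should be named for this outcome, because the present wording attaches mixed models to categorical and ordered variables.

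The cost is a few words and no extra data. The downside is a departure from the three levels now stated. Because recruitment began in January 2017, the change should be dated and made before the symptom results are compared between groups. A patient who stays at 0 will also rank below partial improvement with no room to improve, which is a further reason to keep the levels descriptive.

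### The KPS rule counts only falls of less than 10 points as worsening, so a fall of 10 points or more has no proper category

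*Protocol article*

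**What the plan says.** Section 2.3.2, item 2, of the protocol article makes KPS a secondary outcome with a three-level efficacy grading:

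- Top level: "improved, KPS score increased > 10 points and maintained for more than 4 weeks".
- Middle level: "stable, KPS score no significant change". No number is attached.
- Bottom level: "worsening, KPS score reduced by < 10 points".

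On the granularity of the scale, the same item says: "Practitioners occasionally assign performance scores in between standard intervals of 10". So steps of 10 are the norm and other values the exception. On frequency it says: "The investigators evaluate the KPS score every 3 months using scoring method as summarized in Table 2". Table 2 is not reproduced in the text at hand, but the text cites it for the scoring method and states the three efficacy levels itself. Section 2.5 sets the entry requirement: "KPS score ≥ 60 points". No other section gives a different rule for worsening.

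**The concern.** A category named worsening should collect patients whose score falls materially. As written, it collects only those whose fall is too small to register on the standard steps. The rule also runs backwards: a 5-point dip, possible only with an in-between score, counts as worsening, while a drop from 90 to 40 does not. The only other place for that patient is the stable level, where a 50-point decline would be reported as no significant change.

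At stake is the three-level KPS summary, which is the efficacy measure that the protocol states for this outcome. A comparison of the cohorts on these levels would rest on a bottom category that is nearly empty by construction, with declines either unclassified or counted as stable. Because the stable level has no bound, the five centres or the analysts could also place the same patient differently, or settle the cut-off after seeing the data.

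**Working it through.** There is no stated sample size, power or error rate to reproduce here. The check applies the written rules to every possible pair of scores.

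**Inputs**

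- Baseline KPS: 60 to 100 (section 2.5).
- Follow-up KPS: 0 to 100 (section 2.3.2, item 2).
- Grid: steps of 10 (the standard), then steps of 5 to allow for in-between scores. The 5-point grid is my assumption, since the protocol does not say which in-between values are used.
- d = follow-up score minus baseline score.
- Improved if d > 10. The 4-week maintenance condition is set aside because it does not bear on falls.
- Worsening if −10 < d < 0, the literal reading of a reduction of less than 10.
- Stable if d = 0. This is an assumption, since the text gives no bound.

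**Single changes**

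| Change d | Level as written |
|---|---|
| +20, +15 | improved |
| +10, +5 | none, unless taken as stable |
| 0 | stable |
| −5 | worsening |
| −10, −15, −20, −30, −60 | none, unless taken as stable |

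**All possible falls, 10-point grid**

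Baselines of 60, 70, 80, 90 and 100 allow 6, 7, 8, 9 and 10 falls, and 6 + 7 + 8 + 9 + 10 = 40. The smallest is 10 points, and 10 < 10 is false. Worsening: 0 of 40. No numeric category: 40 of 40.

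**All possible falls, 5-point grid**

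The nine baselines 60, 65, …, 100 allow 12, 13, …, 20 falls, and 9 × (12 + 20)/2 = 144. Only the 5-point fall qualifies, once per baseline. Worsening: 9 of 144. No numeric category: 144 − 9 = 135.

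**With the inequality reversed**

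| Worsening rule | 10-point grid | 5-point grid |
|---|---|---|
| As written, fall < 10 | 0 of 40 | 9 of 144 |
| Fall ≥ 10 | 40 of 40 | 135 of 144 |
| Fall > 10 | 40 − 5 = 35 of 40 | 144 − 9 − 9 = 126 of 144 |

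Under the ≥ 10 rule, the 9 falls left over on the 5-point grid are the 5-point ones, which a bounded stable level would take in. The > 10 rule differs from the ≥ 10 rule only for a fall of exactly 10, which occurs once per baseline (5 pairs on the 10-point grid, 9 on the 5-point grid). That is the smallest standard decline, so the choice between the two rules has to be written down.

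These counts are of possible score pairs. They are not forecasts of the share of patients, which would need the distribution of scores and the frequency of in-between values; the protocol gives neither.

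**The case against.** The strongest reply is that this is one wrong sign in one secondary outcome and that the label makes the intended direction plain. No sensible analyst would file a 40-point fall as no significant change. The KPS scores are recorded in the case report form, so the levels can be re-derived at any time. Section 2.6 also provides repeated-measures analysis of variance and names generalized estimating equations or mixed models for data at several time points. All of this stands as an argument about severity. It does not remove the error: the intended direction is clear but the intended cut-off is not, because ≥ 10 and > 10 treat a 10-point fall differently and the stable level does not settle it. Nor is the sign likely to be an artefact of text extraction, since the inequalities in item 1 of the same section read coherently.

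A reader might infer more than the document supports:

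- **That deterioration would be hidden throughout the trial.** Recurrence and death enter the primary outcomes (section 2.3.1), and ECOG score and QLQ-BR23 are assessed separately every 3 months. Only the three-level KPS summary is distorted.
- **That the improvement threshold is also an error.** Requiring more than 10 points is strict, but it contradicts nothing. A patient who starts at 100 cannot improve under any rule.
- **That the 4-week condition cannot be checked.** A rise still present at the next 3-monthly assessment is a coarse but workable check.
- **That a named test would be invalid.** Section 2.6 lists χ² and rank-sum tests in general terms and ties none of them to KPS.

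**Conclusion.** The point holds. The worsening rule is wrong as written: on the standard 10-point steps it captures 0 of 40 possible falls, and on a 5-point grid 9 of 144. Every fall of 10 points or more is left without a category or placed in an unbounded stable level. The three-level KPS result would then show almost no worsening and would misclassify real declines.

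The conclusion rests on a literal reading of the clause and on the protocol's own statement that steps of 10 are standard and in-between scores occasional. It does not depend on how stable is bounded, because either placement of a large fall is wrong.

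The reach is limited to one secondary outcome. Progression-free survival, overall survival and the sample size are unaffected, and the recorded scores allow full correction. This should be fixed; it does not threaten the trial's main conclusions.

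**What to change.** Rewrite the grading in section 2.3.2, item 2, so that every possible change has exactly one level:

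- **Worsening:** reverse the inequality, for example a decrease of ≥ 10 points from baseline. If > 10 is preferred, to mirror the improvement rule, say so explicitly.
- **Improved:** may stay as it is.
- **Stable:** give a numeric bound covering all remaining changes. With the example above, that is any decrease of less than 10, no change, any increase of up to 10, and any larger increase that is not maintained.

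State the reference score (baseline) and date the correction before the analysis. The cost is one or two sentences. No new data are needed, because the levels are derived from KPS scores already recorded in the case report form.

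### The KPS worsening level is set as a fall of less than 10 points, so a decline of one full scale step or more matches no level

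*Protocol article*

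**What the plan says.** Section 2.3.2, item 2, of the protocol article makes KPS a secondary outcome. It describes a scale that "runs from 100 to 0, where 100 is “perfect” health and 0 is death" and adds: "Practitioners occasionally assign performance scores in between standard intervals of 10". On timing and method it says: "The investigators evaluate the KPS score every 3 months using scoring method as summarized in Table 2". It then sets three levels of efficacy:

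- The top level, for a gain, reads "improved, KPS score increased > 10 points and maintained for more than 4 weeks".
- The middle level, which has no numeric bound, reads "stable, KPS score no significant change".
- The bottom level, for a loss, reads "worsening, KPS score reduced by < 10 points".

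No level is given for a fall of 10 points or more. Section 2.5 admits patients with "KPS score ≥ 60 points". Nothing else in the visible text restates or corrects the worsening threshold. Table 2 is not shown; its caption calls it a KPS symptom assessment table.

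**The concern.** A worsening level should collect the patients who have lost function. This one has an upper limit on the loss and no lower limit, so it admits only falls too small to be a full scale step and shuts out all larger ones. It is not the counterpart of the improved level, which requires a gain above 10 points, and it covers the small changes that a reader would expect to find under stable.

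Patients enter after surgery without recurrence and are followed for recurrence and death, so some decline in performance status can be expected. If the three levels were coded as printed, patients with a real decline would have no level, and the worsening group would hold only trivial falls or nobody. A comparison of the cohorts on these levels would then misstate or omit decline. An analysis plan that copied the protocol's definition would carry the error forward.

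**Working it through.** The protocol gives no figure that depends on this threshold, so there is none to reproduce. The check applies the three levels literally to every possible pair of baseline and follow-up scores.

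**Inputs**
- Scale 100 to 0, with 0 as death; standard steps of 10 (section 2.3.2, item 2).
- Baseline of at least 60 (section 2.5).
- Change d = follow-up score minus baseline score.
- Improved: d > 10. The 4-week maintenance condition is left aside because it does not bear on declines.
- Worsening as written: −10 < d < 0.
- Stable: d = 0. This is an assumption, since the text gives no bound.

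**Standard 10-point scale.** The baselines are 60, 70, 80, 90 and 100. The number of lower scores available from each is 6, 7, 8, 9 and 10, so the possible declines number 6 + 7 + 8 + 9 + 10 = 40. The smallest has d = −10, which does not satisfy −10 < d. Hence 0 of 40 are worsening, and all 40 match no numeric level.

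**With in-between scores.** Assume a 5-point grid for these; the document does not say which intermediate values are used. There are nine baselines (60, 65, …, 100), with 12, 13, …, 20 lower scores available, so the possible declines number 12 + 13 + … + 20 = 144. Only the nine 5-point falls satisfy the rule. The other 144 − 9 = 135 match no numeric level. The falls that qualify are the smallest ones.

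**Fall to 0.** From an eligible baseline this is a fall of 60 to 100 points, so it is never worsening under the written rule.

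**With the inequality reversed (10-point scale)**

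| Worsening rule | Declines classed as worsening |
|---|---|
| As written: fall < 10 | 0 of 40 |
| Fall ≥ 10 | 40 of 40 |
| Fall > 10 (mirror of improved) | 40 − 5 = 35 of 40 |

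The five declines on which the last two rules differ are the one-step falls, one from each baseline.

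These are counts of possible score pairs. They are not forecasts of how many patients would be affected.

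**The case against.** The strongest reply is that this is probably a slip of typing or translation with limited reach. KPS is one of six secondary items. Scores are taken every 3 months and recorded in the CRF. Section 2.6 plans repeated-measures analysis and mixed or estimating-equation models for variables measured over time; it does not name KPS, but nothing restricts KPS to the three levels. ECOG and QLQ-BR23 are assessed at the same 3-month interval, safety is followed separately, and PFS and OS do not use KPS. A coder would probably notice patients without a level. All of this stands and limits the severity. It does not make the printed rule right.

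Three stronger readings are tempting and are not supported:

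- *The study cannot show deterioration in either cohort.* The raw scores and the other outcomes can show it, and even the written rule admits an occasional small fall.
- *Declining patients would be called stable.* That level requires no significant change, which a fall from 90 to 50 does not satisfy. Read literally, the text leaves such a patient unclassified.
- *The error costs a calculable amount of power.* The document gives no KPS decline rates, no share of in-between scores and no power target for KPS, so any such figure would rest on invented inputs.

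It can also be said that Table 2 might clarify the matter. Its content cannot be checked, but the text cites it for the scoring method, while the three levels are set out in full in the text itself.

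**Conclusion.** Wrong as written, in a secondary outcome; moderate severity. On the standard 10-point scale, 0 of 40 possible declines from eligible baselines meet the worsening rule, and every fall of a full step or more, including a fall to 0, matches no numeric level. The three-level KPS classification therefore misclassifies or omits real decline.

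The 0-of-40 result needs only the scale and the entry criterion as stated. Two assumptions enter elsewhere: the 9-of-144 figure rests on a 5-point grid for in-between scores, and reading stable as zero change is what leaves the larger falls without any level. A looser bound on stable would not bring any of them into worsening.

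The document does not settle whether the intended bound was at least 10 or more than 10, nor whether deaths are to be scored in this outcome at all.

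**What to change.** In section 2.3.2, item 2, and in the matching CRF and analysis coding:

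1. Reverse the inequality. Worsening becomes either a fall of at least 10 points, which counts a one-step fall, or a fall of more than 10 points, which mirrors the improved level and leaves one-step falls to stable. The sponsor must choose one and state it.
2. Define stable as every change that is neither improved nor worsening, so that each patient with a baseline and a follow-up score has exactly one level.
3. State how deaths are handled: scored as KPS 0 and counted as worsening, or left to OS and excluded from this classification by a stated rule.
4. Recode patients already enrolled from their recorded scores.

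This should be settled before cohort results are examined, because the two bounds treat every one-step fall differently and a choice made afterwards would be post hoc. The cost is a short text correction and a recoding step. No new data, visits or patients are needed, and the sample size does not change.
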